### Recruitment {15}

Participants in this trial will be recruited from The Fourth Affiliated Hospital, Zhejiang University School of Medicine.

## Assignment of interventions: allocation

### Sequence generation {16a}

Patients will be randomized (using a random number table generated by the Excel RANDOM function) to group A or B. A fixed data analyst will generate the table of random numbers via computer.

### Concealment mechanism {16b}

The allocation sequence will be securely stored in sequentially numbered, opaque, sealed envelopes. Once the consent form is completed, the allocation will be revealed to the investigator.

### Implementation {16c}

The randomization scheme will be hidden from doctors and patients.

## Assignment of interventions: blinding

### Who will be blinded {17a}

Patients will be randomized (using a random number table generated by the Excel RANDOM function) to group A or B. A fixed data analyst will generate the table of random numbers via computer. The randomization scheme will be hidden from doctors and patients. Since the intervention in this trial could not blind the doctors, the data analyzers and patients were blinded.

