#### Extracorporeal fenestration

Based on the preoperative CTA reconstructions, the diameter of the aorta and branch vessels, lengths, angles to the arch, clock positions, and related relationships are measured, and a preoperative design for the fenestrations is developed. The outer sheath of the stent graft (Ankura, Lifetech, Inc., Shenzhen, China) is then pushed back for several centimeters under sterile conditions, allowing the proximal portion of the stent graft to be released [14]. The length of the released segment should be 1 to 2 cm distal from the location of fenestration [14]. Using a sterile ruler, the location of the fenestration is determined in accordance with the preoperative plan. The 12 o’clock position is considered to be at the front of the trigger. The position of the stent graft relative to the trigger is also referred to as the 12 o’clock position. If the fenestration must avoid stent struts, then the fenestration is deemed to be at 12 o’clock, as is the position of the trigger relative to the stent graft. The fenestration can be created using scissors or a cautery device. The fenestration can be strengthened using the loop of a snare [14, 15]. To indicate the position of the fenestration during the DSA, either the original mark in the stent graft or an extra marker can be sutured to the fenestration [16]. After passing the aortic arch, the fenestration mark is aligned with the branch artery’s corresponding position. After deployment of the stent graft, a 0.018-inch guidewire is advanced through the fenestration. Deployment of stent in the branch artery.

Follow-up appointments are scheduled at 1, 6, and 12 months after surgery. An aortic CTA will be required for every follow-up.

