### Outcomes {12}

In this trial, the outcomes will be developed according to the standard clinical endpoint of endovascular aortic repair [17]. The primary outcome will be the all-cause mortality (30 days). The secondary outcomes will include incidence of secondary intervention (30 days, 6 months, 1 year), incidence of endoleak (30 days, 6 months, 1 year), incidence of major adverse events (MAE) (i.e., immediate procedural success and complications) (30 days, 6 months, 1 year), immediate technical success rate, and all-cause mortality (6 months, 1 year). All-cause mortality is the annual number of deaths in a given group per the population in that group. Endoleak was assessed by DSA angiography during surgery and by CTA and DUS after surgery. We recommend re-intervening to achieve a proper seal in patients with type I or type III endoleaks following TEVAR according 2024 ESC Guidelines [18]. We recommend to perform 30-day imaging after TEVAR, by CTA and DUS, to assess the success of intervention. A secondary intervention will be performed if necessary, based on the follow-up results and the patient’s condition.

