### Procedure for unblinding if needed {17b}

Given the nature of our intervention, which involves extracorporeal fenestration and in situ fenestration, our study is designed as an unblinded trial.

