## Data collection and management

### Plans for assessment and collection of outcomes {18a}

Baseline data will be collected after participants have signed informed consent. For the experimental group, intervention-related data will be obtained from the electronic medical records system within 30 days after patient discharge. Follow-up data will be obtained through outpatient visits or telephone interviews after the participants have completed each follow-up aortic CTA examination.

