### Data management {19}

Data will be collected in case report forms (CRF), including demographic characteristics, symptoms, signs, laboratory tests, medication, complications, and morphological outcomes. All the CRFs will be filled out independently by one researcher and checked by another researcher. All data collected during the study will be kept for 3 years after the completion of the study.

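### Masking is limited to patients and analysts, so follow-up CTA and DUS can be read for endoleak with the arm known; no masked reading is provided for

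*Protocol article*

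**What the plan says.** The protocol article assigns masking in {17a}: "Since the intervention in this trial could not blind the doctors, the data analyzers and patients were blinded". The next section, {17b}, says that "our study is designed as an unblinded trial". In the Discussion, the limitation on blinding is stated for surgeons only.

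Endoleak is a secondary outcome at 30 days, 6 months and 1 year (Outcomes {12}). On method, the same section says: "Endoleak was assessed by DSA angiography during surgery and by CTA and DUS after surgery". It then links the imaging to a further secondary outcome: "A secondary intervention will be performed if necessary, based on the follow-up results and the patient’s condition".

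The intervention section adds: "An aortic CTA will be required for every follow-up". Section {18a} describes collection: "Follow-up data will be obtained through outpatient visits or telephone interviews after the participants have completed each follow-up aortic CTA examination". Section {19} describes data entry: "All the CRFs will be filled out independently by one researcher and checked by another researcher". None of these sections says who reads the images or whether the reader, collector or CRF researcher knows the arm. Radiologists are mentioned only as members of the data monitoring committee ({21a}).

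**The concern.** The operating surgeon must know the technique. The person who reads a CTA a month or a year later need not. By treating doctors as one group that cannot be masked, {17a} gives up masking where it is at least partly attainable, and for the outcome that most needs it among those read from images.

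Calling an endoleak present or absent involves judgement when the finding is equivocal. If the reader knows the arm, equivocal findings may be called differently in the two groups. Masking the data analyst does not repair this, because the outcome is already fixed when it reaches the analyst. The reading also contributes to the decision on secondary intervention, so one distorted judgement can affect two secondary outcomes.

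Readers may hold prior views. The Background cites work that questions the stability of non-reinforced fenestrations and, with it, the in situ procedure. It also reports favourable short-term results for both techniques, so no direction of bias can be predicted from it.

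**Working it through.** **Comparing the sections**

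1. {17a} is a closed list with a reason: patients and analysts are masked, doctors are not because the intervention prevents it.
2. The Discussion states that constraint for surgeons. It does not extend to a reader who took no part in the operation, so {17a} is wider than its reason.
3. {17b} describes the trial as unblinded without exception. That conflicts with {17a} and provides no masking for readers either.
4. {12}, {18a} and {19} set out how endoleak is assessed, collected and entered, and contain no masking step. Under {16b}, the allocation is revealed to the investigator after consent.
5. So a team that follows the article as written may have the arm known at the reading, and nothing prevents operators from scoring their own patients.

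**Possible size, on assumptions**

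The article gives no endoleak rate and no reading accuracy, so it has no figure on this point to reproduce. Its sample size is built on 30-day mortality and does not change with reader masking. The only input from the article is 170/2 = 85 per arm; all rates below are assumed.

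Observed rate = true rate × sensitivity + (1 − true rate) × false-call rate.

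One error in one arm, with a true rate of 15% in both arms and otherwise perfect reading:

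- Equivocal leaks dismissed, sensitivity 80%: 0.15 × 0.80 = 12.0% against 15.0%, a false difference of 3.0 points.
- Leak-free scans over-called at 5%: 0.15 + 0.05 × 0.85 = 19.25% against 15.0%, a false difference of about 4.3 points.
- Standard error of the difference: √(2 × 0.15 × 0.85 / 85) = 0.055, or 5.5 points. The shifts are about 0.55 and 0.78 of this.

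Errors in both directions at once, with equal true rates, 85 per arm and a two-sided 5% normal-approximation test:

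| True rate | Sensitivity, A vs B | False calls, A vs B | Observed, A vs B | False difference | Chance of P < 0.05 |
|---|---|---|---|---|---|
| 5% | 80% vs 95% | 2% vs 5% | 5.9% vs 9.5% | 3.6 points | 14.3% |
| 10% | 80% vs 95% | 2% vs 5% | 9.8% vs 14.0% | 4.2 points | 13.5% |
| 20% | 80% vs 95% | 2% vs 5% | 17.6% vs 23.0% | 5.4 points | 14.2% |
| 5% | 70% vs 95% | 2% vs 10% | 5.4% vs 14.3% | 8.9 points | 50.0% |
| 10% | 70% vs 95% | 2% vs 10% | 8.8% vs 18.5% | 9.7 points | 46.0% |
| 20% | 70% vs 95% | 2% vs 10% | 15.6% vs 27.0% | 11.4 points | 45.0% |

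The arm labels are arbitrary. With equal accuracy in both arms (sensitivity 90%, false calls 5%), the false difference is zero and the chance of P < 0.05 stays at 5%.

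**The case against.** The strongest objection is that this rests on silence in a condensed article. A full protocol is available on request ({31c}), and the identity of readers and the content of request forms are details that an article commonly leaves to it. That holds for the reading procedure. It does not hold for the masking scheme, because {17a} lists who is masked and explains who is not, and {17b} calls the trial unblinded. The point rests on those statements.

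Three further objections stand and limit the point:

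- A reader might infer that endoleak will in fact be judged with the arm known at every visit. No reader is named, so the article supports only that it can be.
- A reader might also infer that staff already in place could be masked at almost no cost. The article states no readers, staffing or cost. If operators read their own patients' scans, someone else would have to be found.
- The single-error shifts are smaller than the sampling error. The larger figures need strong arm-dependent error in both directions, for which the documents offer no evidence.

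Masking would also be imperfect. The extracorporeal technique may leave a sutured marker or a snare loop that identifies the arm on CTA, and intraoperative DSA cannot be masked. Partial masking still removes the request form, the operation note and self-reading by operators as sources of knowledge of the arm.

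**Conclusion.** The concern holds in a limited form. The masking scheme in {17a} is wider in what it gives up than its reason allows, it conflicts with {17b}, and it leaves a reader-judged secondary outcome at three time points open to assessment with the arm known. Secondary intervention may be affected through the reading, although it also depends on the patient's condition.

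The amount of bias cannot be established from the documents. The assumed single-error shifts of 3 to 4.3 points lie below one standard error (about 5.5 points), so neither alone would usually produce a false significant difference. The combined-error cases show what is possible, not what is likely.

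It would be wrong to conclude that the main result is compromised. All-cause mortality at 30 days does not depend on a reader. The amendment is worth making, but the validity of the primary comparison does not depend on it.

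**What to change.** Amend {17a} as follows:

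- For the trial endpoint, postoperative endoleak on CTA and DUS is reported by existing readers who did not perform the procedure, from a request that omits the arm and the operation note, as far as the images allow.
- That report is entered in the CRF before the arm is linked, within the two-researcher entry process of {19}.
- Intraoperative DSA and immediate technical success are declared unmasked, and markers or snare loops are named as reasons why masking may be incomplete.
- {17b} is reconciled with {17a}, so that the article says once, and consistently, who is masked.

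The change needs protocol wording and a request form without the allocation. It alters no sample size, visit or treatment, and clinical readers can still obtain the operation note when care requires it. The downside is that masking is only partial. The fix also assumes that non-operating staff already read the scans. The article does not state this, so the trial team should confirm it first; if it is not so, a further reader is needed.

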### Procedure for unblinding if needed {17b}

Given the nature of our intervention, which involves extracorporeal fenestration and in situ fenestration, our study is designed as an unblinded trial.

## Data collection and management

### Plans for assessment and collection of outcomes {18a}

Baseline data will be collected after participants have signed informed consent. For the experimental group, intervention-related data will be obtained from the electronic medical records system within 30 days after patient discharge. Follow-up data will be obtained through outpatient visits or telephone interviews after the participants have completed each follow-up aortic CTA examination.

### Plans to promote participant retention and complete follow-up {18b}

A researcher will proactively remind participants of their scheduled CTA follow-up appointments via telephone.

### Data management {19}

Data will be collected in case report forms (CRF), including demographic characteristics, symptoms, signs, laboratory tests, medication, complications, and morphological outcomes. All the CRFs will be filled out independently by one researcher and checked by another researcher. All data collected during the study will be kept for 3 years after the completion of the study.

### Confidentiality {27}

Data access will be strictly limited to the designated study researchers. Any personal information collected during the trial will be treated with utmost confidentiality and handled in strict adherence to the pertinent legal provisions.

### Plans for collection, laboratory evaluation, and storage of biological specimens for genetic or molecular analysis in this trial/future use {33}

Not applicable; no biological specimens will be collected for this trial.

## Statistical methods

### Statistical methods for primary and secondary outcomes {20a}

Baseline characteristics and clinical outcomes will be expressed as numbers (percentages) for categorical variables and mean ± standard deviation for continuous variables. The chi-square test or Fisher’s exact test will be used to analyze categorical variables, and the independent *t*-test or the Wilcoxon signed-rank test will be adopted to analyze continuous variables. The Kaplan–Meier method will be performed to generate survival curves, and the log-rank analysis will be used to compare the differences between survival curves. Multivariate Cox regression adjusted by centers will be applied to calculate the hazard ratio risk. *P* < 0.05 will be considered to indicate statistical significance.

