## Trial design {8}

The study design is a prospective, single-center, non-inferiority, randomized controlled trial. A total of 170 eligible participants will be divided randomly into two groups in a ratio of 1:1.

The flowchart of the trial is presented in Fig. 1.

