### Sample size {14}

The power of the trial is calculated as two co-primary endpoints, sharing a combined *α*-level of 0.05. According to the literature, cumulative 30-day all-cause mortality was similar in both groups: 3.8% [8]. An equal (1:1) equivalence design was used, with *α* = 0.05 (two-sided), *β* = 0.20 (two-sided), Δ = 10%, from which the sample size *n* was estimated. In accordance with the design of the trial and the primary efficacy outcome measures, the sample size was estimated using the following formula:$$n=\frac{\pi_t\times\;\left(1-\pi_t\right)\;+\;\pi_c\;\times\;\left(1-\pi_c\right)}{\left(\mathit\triangle\mathit\;\mathit-\mathit\;\mathit{\left|{\pi_t-\pi_c}\right|}\right)^2}\times\left(\mu_{\mathit a\mathit/\mathit2}\mathit+\mu_{\mathit\beta}\right)^2$$

A minimum of 154 patients (77 per group) will need to be recruited. However, considering a potential dropout rate of 10%, combined with the low probability of adverse events in this trial, the total sample size was expanded to 170 patients.

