### Methods for additional analyses (e.g., subgroup analyses) {20b}

Two prespecified subgroup analyses of age (18–49 vs. 50–80) and gender will be conducted for the primary outcome by adding an interaction term (e.g., age × group) into the Cox regression model. A sensitivity analysis will be conducted for the primary outcome based on the per-protocol set, which included patients who adhered to the treatment and follow-ups. Continuous data will be compared using the Student *t*-test or Mann–Whitney *U* test for parametric and non-parametric data, respectively. Categorical data will be compared using the chi-square test or Fisher’s exact test, as appropriate. Since the participants might crossover or be lost to follow-up, non-inferiority will be tested using two analysis sets. One set is the intention-to-treat (ITT) set, which includes all patients as randomized, regardless of whether they received the assigned treatment. The other is the per-protocol (PP) set. *P* < 0.05 will be considered statistically significant, and all data will be analyzed using SAS 9.2 software.

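### The methods stated for the primary outcome are only tests of no difference at P < 0.05; the 10-point margin is not tied to any test or interval, so the stated analysis cannot support the planned non-inferiority conclusion

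*Protocol article*

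**What the plan says.** - **Design.** Trial design {8}: "The study design is a prospective, single-center, non-inferiority, randomized controlled trial". Outcomes {12} makes 30-day all-cause mortality the primary outcome.
- **Margin.** Sample size {14} assumes that "cumulative 30-day all-cause mortality was similar in both groups: 3.8" per cent, with Δ = 10%, α = 0.05 two-sided and β = 0.20. It calls the design an equivalence design. Δ appears nowhere else in the protocol.
- **Methods for primary and secondary outcomes {20a}.** For proportions, chi-square or Fisher's "exact test will be used to analyze categorical variables". For survival, "the log-rank analysis will be used to compare the differences between survival curves". For modelling, "Multivariate Cox regression adjusted by centers will be applied to calculate the hazard ratio risk". For continuous data, the t-test or "the Wilcoxon signed-rank test will be adopted to analyze continuous variables". The threshold is P < 0.05, with no margin and no confidence bound.
- **Additional analyses {20b}.** It says "non-inferiority will be tested using two analysis sets", intention-to-treat and per-protocol, and repeats chi-square/Fisher and P < 0.05.
- **Non-adherence and missing data {20c}.** Extracorporeal fenestration will be declared non-inferior to in situ fenestration only if this is shown in both sets. How it is to be shown is not stated.

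**The concern.** A non-inferiority claim means rejecting the hypothesis that the new technique is worse by at least the margin. Chi-square, Fisher and log-rank address a different hypothesis, that the arms are equal. The Cox model yields a hazard ratio, while Δ in {14} is an absolute difference in proportions, so no {20a} result can be compared with the 10 points as written.

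The trial's one confirmatory claim therefore has analysis sets and a both-sets rule, but no stated test. An analysis that follows {20a} gives a P value that does not answer the question in {20c}. If the test is chosen after outcome data are seen, the choice can affect the result, because with so few deaths the available methods differ noticeably in both error and power.

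**Working it through.** **Inputs.** 30-day mortality 3.8% in each arm, Δ = 10 points, α = 0.05 two-sided, β = 0.20 (described as two-sided), 77 per group before dropout and 170 in total (85 per group); all from Sample size {14}. Expected deaths in 170 patients: 0.038 × 170 = 6.5.

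**1. The plan's own figure.** The formula in {14} with equal rates is n = 2π(1 − π)/Δ² × (z_α/2 + z_β)².
- 2 × 0.038 × 0.962/0.10² = 7.311.
- With z = 1.960 and 1.282 (β taken as two-sided, as stated): 7.311 × 10.507 = 76.8, so 77 per group. This reproduces the 154.
- With z = 0.842 for β, as the formula is printed: 7.311 × 7.849 = 57.4, so 58 per group. That is a separate matter. What counts here is that the sample size is built on the 10-point difference in proportions.

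**2. The listed tests when the techniques are equal** (exact binomial enumeration, 3.8% in both arms, 85 per group, chi-square uncorrected).
- P ≥ 0.05: Fisher 0.988, chi-square 0.956.
- P < 0.05 in either direction: 1.2% and 4.4%. By symmetry only about half of these, 0.6% and 2.2%, favour extracorporeal fenestration, the one result of these tests that would imply its non-inferiority.

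**3. The listed tests when extracorporeal fenestration is worse by the full margin** (13.8% vs 3.8%). Probability that P ≥ 0.05:

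| Per group | Fisher | Chi-square |
|---|---|---|
| 77 | 0.497 | 0.374 |
| 85 | 0.436 | 0.343 |

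These are false-acceptance rates only under the supposition that a non-significant result is taken as non-inferiority.

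**4. A margin-based rule.** Non-inferiority is shown if the upper limit of the two-sided 95% CI for the risk difference is below 0.10.

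| Per group | Method | Shown at 3.8% vs 3.8% (power) | Shown at 13.8% vs 3.8% (error) |
|---|---|---|---|
| 77 | Wald | 88.5% | 3.6% |
| 77 | Score (Farrington–Manning) | 78.3% | 2.2% |
| 85 | Wald | 90.5% | 3.4% |
| 85 | Score (Farrington–Manning) | 83.9% | 2.4% |

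The Newcombe interval gives the same figures as the score method in these four cases.

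**5. An example.** Deaths 8/85 (extracorporeal) vs 3/85 (in situ) give Fisher P = 0.21. The difference is 5/85 = 5.9 points with standard error √(0.0941 × 0.9059/85 + 0.0353 × 0.9647/85) = 0.0375. The Wald upper limit is 0.0588 + 1.96 × 0.0375 = 0.132, and the Newcombe limit is 0.143. Fisher finds no significant difference, while non-inferiority at 10 points is not shown.

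**The case against.** **The sentence in {20a} is generic.** It speaks of categorical variables at large, covers baseline data too, and does not name chi-square or Fisher as the test of the primary hypothesis. The choice of statistic and interval is often left to a statistical analysis plan. This stands in part: silence on Wald versus score would be no finding. But the section is headed as the methods for the primary outcome, names tests for it and sets a threshold, and {20b} repeats both. An analysis plan that followed it would inherit the mismatch; one that used the margin would depart from it.

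**The protocol does plan a non-inferiority test.** {20b} and {20c} say so, and {20c} adds a strict both-sets rule. That stands, so the protocol is not silent on the aim. These sections settle who is analysed and in how many sets, but not the criterion.

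**Stronger readings that the document does not support.**
- A reader might infer that a non-significant P will be declared non-inferiority. Nothing says so, and {20c} requires non-inferiority to be shown. The 34% to 50% figures are conditional on that misuse.
- A reader might take P < 0.05 as a one-sided non-inferiority threshold, which would give an error at the margin of 4.9% with the score test at 77 per group. No section calls it one-sided, and {14} states a two-sided α.
- A reader might count the centre adjustment and the signed-rank test as further threats to the primary result. They are not. Adjusting for centre in a single-centre trial leaves the Cox model effectively unadjusted. The signed-rank test is for paired data, but every outcome in {12} is an incidence or a rate, and {20b} already names Mann–Whitney.

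**Conclusion.** The point holds as a mismatch between the declared hypothesis and the stated analysis. The methods in {20a}, echoed in {20b}, test for no difference at P < 0.05, and the 10-point margin in {14} is never linked to a test or an interval. The conclusion planned in {20c} cannot be reached from them, except in the rare case of a significant result favouring extracorporeal fenestration. With equal mortality of 3.8% and 85 per group, P ≥ 0.05 in 98.8% (Fisher) or 95.6% (chi-square) of trials, whereas a margin-based interval would show non-inferiority in 83.9% (score) or 90.5% (Wald).

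Assumptions: 3.8% in both arms, as in {14}; no losses; and a one-sided error of 2.5%, which is what the two-sided 0.05 implies. {14} also speaks of two co-primary endpoints sharing α and of an equivalence design, so the level for the mortality endpoint is not fully settled. The mismatch does not depend on that level. It should be corrected before outcome data are analysed.

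**What to change.** In {20a}, state that the primary analysis is the difference in 30-day death proportions, extracorporeal minus in situ, and that non-inferiority is shown if the upper limit of the two-sided 95% CI lies below +10 percentage points in both sets named in {20c}. Keep the listed tests for the other comparisons.

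Two passages need to agree with this wording:
- The direction follows {20c}. The closing paragraph of the Discussion states the reverse (in situ non-inferior to extracorporeal) and must be reconciled.
- {20c} also describes a modified intention-to-treat analysis of the primary outcome, whereas {20b} defines intention-to-treat as all patients randomised. The criterion should say which set it uses.

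A score-type interval is a suggestion, because deaths are rare: its error at the margin is 2.2% against 3.6% for Wald at 77 per group. Its cost is power: 78.3% against 88.5% at 77 per group, and 83.9% against 90.5% at 85. With 77 evaluable patients per group, power falls just under the 80% that β = 0.20 conventionally implies, so the choice should be made knowingly and recorded in advance.

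Tidy-ups with no bearing on the primary conclusion: delete the centre adjustment, and replace the signed-rank test with the Mann–Whitney test already named in {20b}.

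The criterion itself is a change of wording and needs no new data or procedures. The only real trade-off is the power cost if the score interval is chosen.

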## Methods: participants, interventions, and outcomes

### Study setting {9}

The current study will take place in The Fourth Affiliated Hospital of Zhejiang University School of Medicine in China.

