## Discussion

TEVAR for thoracic aortic pathologies involving the aortic arch provides a feasible and effective approach for such diseases and has been widely used both in the world. However, it still faces great challenges [10]. The Society for Vascular Surgery Practice Guidelines suggest routine preoperative revascularization in patients who need elective TEVAR where achievement of a proximal seal necessitates coverage of the left subclavian artery [8]. Extracorporeal fenestration and in situ fenestration techniques were initially conceived to overcome emergency or as a bail out, but in point of fact 60% or more of indications have turned out to be elective, echoing broad acceptance of the treatment and, one can suppose, its effectiveness [19, 20].

Several studies have demonstrated the safety and effectiveness of extracorporeal fenestration and in situ fenestration in patients with aortic disease involving the left subclavian artery [4–7]. However, extracorporeal fenestration or in situ fenestration techniques which is the best choice were unknown.

However, our study has several limitations. First, the surgeons cannot be blinded to the intervention. Second, the sample size is still relatively small, although we have calculated it. This was a single-center clinical trial, and multicenter clinical trials should be considered. Another limitation is that the postoperative follow-up time is short. Therefore, a worldwide large-scale clinical trial is still warranted in the future.

In summary, this study will compare the safety and validity of extracorporeal fenestration and in situ fenestration in patients with aortic disease involving the left subclavian artery. If in situ fenestration is non-inferior to extracorporeal fenestration in patients with aortic disease involving the left subclavian artery, this trial could contribute to future updates of clinical guidelines for these patients.

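### Three stated analyses do not fit the design: centre adjustment in a one-centre trial, a paired rank test for independent arms, and Cox interaction tests on about six deaths

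*Protocol article*

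**What the plan says.** **Centre.** Section {20a} of the Protocol article states: "Multivariate Cox regression adjusted by centers will be applied to calculate the hazard ratio risk". Trial design {8} states: "The study design is a prospective, single-center, non-inferiority, randomized controlled trial". Study setting {9} names one hospital, and the Discussion lists the single centre as a limitation: "This was a single-center clinical trial, and multicenter clinical trials should be considered".

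**Rank test.** In {20a}, the non-parametric partner of the independent t-test is given as follows: "the Wilcoxon signed-rank test will be adopted to analyze continuous variables". In {20b}, the Student t-test and Mann–Whitney U are paired instead, as the "test for parametric and non-parametric data, respectively".

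**Subgroups.** Section {20b} plans two subgroup analyses, by age (18–49 against 50–80) and by gender. It says that they "will be conducted for the primary outcome by adding an interaction term" to the Cox model. Outcomes {12} fixes the primary outcome as all-cause mortality at 30 days. Sample size {14} takes this as 3.8% in both groups and arrives at 154 patients, raised to 170. Section {20b} closes with a significance threshold of P < 0.05 and does not mark the subgroup analyses as descriptive.

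**The concern.** Each of these is an instruction that the document gives, not a detail left to a later analysis plan.

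- A covariate with one level carries no information. Centre is also the only adjustment variable the article names, so the sentence as written defines no usable adjustment.
- The signed-rank test works on within-pair differences. Two randomized parallel arms have no pairs, and the two sections disagree about which test applies.
- An interaction contrast needs deaths in all four treatment-by-subgroup cells. At a 30-day mortality of 3.8% that is more likely to fail than not. Software may then still print a very large finite coefficient with a Wald P value, which could be reported as a result. Where the coefficient can be estimated, a non-significant test could be misread as evidence that the treatment effect is the same across age or gender.

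**Working it through.** **Inputs.** Mortality of 3.8% in both groups, minimum 154 and final 170 patients, margin 10%, α = 0.05 two-sided and β = 0.20 marked two-sided (all Sample size {14}); 1:1 allocation (Trial design {8}); two-level subgroups (section {20b}). Subgroup sizes are not given, so the splits below are assumptions.

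**1. The plan's own figure.** Using the printed formula with both rates 0.038, and reading the two-sided β as z = 1.282:

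n = [2 × 0.038 × 0.962 / 0.10²] × (1.960 + 1.282)² = 7.311 × 10.51 ≈ 76.8, so 77 per group and 154 in total. Then 154 × 1.10 = 169.4, so 170. The figure reproduces, which confirms that 3.8% and 170 are the planning values to carry forward.

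**2. Expected deaths.** 170 × 0.038 = 6.46, and 154 × 0.038 = 5.85. The 95% binomial range at 170 is 2 to 12 deaths. With even subgroups there are four cells, each with 6.46 / 4 = 1.615 expected deaths.

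**3. Chance of at least one empty cell.** Treat the cells as independent Poisson counts with means m₁ to m₄. Then P(any zero) = 1 − Π(1 − e^(−mᵢ)).

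| Subgroup split | Cell means (each in both arms) | P(any zero), Poisson | P(any zero), binomial |
|---|---|---|---|
| 50/50 | 1.615, 1.615 | 1 − 0.801⁴ = 59% | 58% |
| 30/70 (assumed) | 0.969, 2.261 | 1 − (0.620 × 0.896)² = 69% | 68% |
| 20/80 (assumed) | 0.646, 2.584 | 1 − (0.476 × 0.925)² = 81% | 80% |

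With 154 patients and even subgroups the binomial figure is 64%. For equal mortality in all cells, the even split is the most favourable case.

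**4. Precision when all four cells have deaths.** The variance of the log ratio of hazard ratios is about the sum of 1/deaths over the four cells. This is smallest when D deaths are spread evenly, at 4 × (4/D) = 16/D. With D = 6, SE = √(16/6) = 1.63.

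- Power for a ratio of hazard ratios of 2: Φ(0.693/1.63 − 1.96) ≈ 6%.
- Power for a ratio of 4: Φ(1.386/1.63 − 1.96) ≈ 13%.
- Ratio needed for 80% power: exp[(1.96 + 0.84) × 1.63] ≈ 97.

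**5. What an empty cell does and does not break.** Take deaths of 2, 2, 2 and 0 in four cells of equal size. Arm totals are 4 and 2, so a main-effects model gives a finite hazard ratio near 2/4 (log −0.69). Only the product term diverges. A main-effects model fails when a whole arm or a whole subgroup level has no deaths. For the arms that chance is 1 − (1 − 0.962⁸⁵)² = 1 − (1 − 0.037)² ≈ 7%.

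**6. Reach of the rank-test error.** The outcomes listed in Outcomes {12} are mortality, incidences and a success rate. None is continuous, so the signed-rank wording reaches only baseline and other continuous data.

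**The case against.** The best defence is that little of this reaches the trial's conclusion.

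- A constant centre term changes no estimate. The word multivariate in {20a} may point to other covariates, whose list an article can leave to the full protocol or analysis plan. This stands. A reader might infer that the adjusted hazard ratio would in fact be unadjusted, but the document does not settle that.
- The signed-rank wording sits beside the independent t-test, and {20b} names Mann–Whitney U, so the intention is clear. A paired test would not run on arms of unequal size, so the slip would probably be caught. This also stands and limits the harm, but it does not make the stated test right.
- A reader might infer that the main Cox model in {20a} is also fitted to 30-day mortality and breaks down whenever one cell is empty. Neither part is supported. Section {20a} covers primary and secondary outcomes and does not say which one the Cox model serves, and mortality at 6 months and 1 year is among the secondary outcomes. As step 5 shows, one empty cell leaves a main-effects model finite.
- Even with an empty cell the likelihood is bounded, so a likelihood-ratio interaction test exists. In the 2, 2, 2, 0 example the main-effects fit is 8/3, 4/3, 4/3, 2/3, and the statistic is about 2 × [2 ln(0.75) + 4 ln(1.5)] ≈ 2.1, below the 5% critical value of 3.84. So the analysis is not strictly impossible. But the article plans an interaction term in a Cox model and does not specify this test, which has too few deaths to be informative.
- The Discussion already admits a relatively small sample. That is a general caveat and does not label these tests as exploratory.

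**Conclusion.** The point holds for all three items, with a modest effect on the main conclusion.

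The centre phrase contradicts the single-centre design but has no numerical effect. The signed-rank test is the wrong test and conflicts with {20b}; its reach is baseline and other continuous data. The interaction analyses are the substantive part, because {20b} ties them expressly to the 30-day primary outcome. On the plan's own 3.8% there is about a 59% chance that the coefficient diverges for an evenly split subgroup, and 69% or 81% under the assumed 30/70 or 20/80 splits. Where it can be estimated, power is about 6% for a ratio of hazard ratios of 2, taking six evenly spread deaths. These figures assume equal mortality in all four cells; a different overall death rate would move them.

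The documents do not support extending this to the main Cox model, or to a limit on the number of covariates at 12 months, since no 12-month death rate is given. The non-inferiority comparison does not depend on centre, the signed-rank test or the interaction terms.

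**What to change.** 1. In {20a}, delete the adjustment by centre. If other covariates are intended, name them.
2. In {20a}, replace the signed-rank test with the Wilcoxon rank-sum (Mann–Whitney) test, so that it agrees with {20b}.
3. In {20b}, replace the two Cox interaction tests for 30-day mortality with deaths/N by arm and the risk difference with a score confidence interval in each age and gender subgroup, labelled descriptive. If a model is wanted, use a Firth-penalised model with treatment, subgroup and their product only. It gives finite estimates when a cell is empty, but the intervals will still be very wide.

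The cost is a few changed sentences and minor programming, with no change to sample size or data collection. The downside is that there will be no conventional interaction P value for the primary outcome.
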